Patients will be excluded if they fail to attend scheduled telerehabilitation sessions or respond to WhatsApp communication. Those experiencing unexpected medical complications, such as infections or cardiac or respiratory events, will be instructed to discontinue the program and withdraw from the study. The exclusion criteria also included changes in clinical status leading to surgical contraindications or new injuries during the prehabilitation period that prevented participation in home exercises. Additionally, participants with cognitive deficits were excluded based on the Portuguese version of the Mini-Mental State Examination (MMSE), with cut-off scores of ≤20 for illiterate individuals, ≤25 for primary school level, ≤26.5 for junior high school, ≤28 for high school, and ≤29 for higher education [15].

Randomization

After the explanatory meeting, eligible participants who complete baseline assessments will be randomized using simple randomization with a 1:1 allocation ratio via Randomizer® (www.randomizer.org). The allocation sequence will be generated by an independent researcher not involved in enrollment or assessment. Allocation concealment will be ensured using sequentially numbered, opaque, sealed envelopes, which will be opened only after confirming participant eligibility.

Control group

The participants in the control group will receive an institutional educational booklet containing standard preoperative physiotherapy recommendations. The only exercise instructions before TKA provided in the booklet were as follows: “(1) Move your feet up and down 20 times (active movement while lying on a treatment table, plantar dorsiflexion) and (2) inhale deeply through your nose while raising your arms and exhale through your mouth as you lower them. Perform 20 repetitions.” Participants in the control group will only follow these institutional procedures and will not engage in a home-based program. They will be instructed to maintain their usual daily activities and adhere to the recommendations provided in the booklet.

Experimental group

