Patients in the experimental group will receive the institutional booklet and participate in a semi-supervised home-based prehabilitation program. Before starting, they will undergo theoretical and practical instruction to ensure proper exercise execution, as outlined in Table 1. Additional time will be allocated during the initial phase to overcome individual digital barriers, and all participants in the intervention group will receive in-person training on how to access video calls, send messages, and interact with the WhatsApp platform. The research team will verify movement accuracy, provide guidance to family members for additional support, and monitor any changes in the participants' physical or mental conditions. The training protocol was designed for a home setting without the need for specialized equipment and was adapted from the tele-prehabilitation model proposed by Guida et al. [16]. It consists of (1) warm-up, (2) balance exercises, and (3) muscle strengthening exercises. Sessions will be conducted three times per week over eight weeks, with at least 48 hours of rest between sessions, totaling a maximum of 24 training sessions.

**Table 1 TAB1:** Home-based exercise protocol. *Estimated time.

	Exercise	Sets	Repetitions	Rest	Time*
Warm-up					
	Seated knee flexion and extension	3	10 movements per leg	No rest	2 min
	Marching in place	3	30 movements	30 s	4 min
Balance					
	Single-leg stance	3	15 s per side	30 s	3 min
	Tandem walking (heel-to-toe)	3	10 steps in each direction	30 s	5 min
Strength					
	Sit-to-stand	3	10	30 s	5 min
	Wall calf raises	3	10	30 s	5 min

To enhance adherence and technique, participants will receive a link to an instructional video (Video 1) and a training diary to log their weekly exercise frequency (Table 2 of Appendices). Additionally, weekly videoconference sessions provide real-time feedback, while WhatsApp monitoring facilitates communication, allowing participants to ask questions via text, images, audio, or video messages. WhatsApp was selected because of its accessibility and ease of use. To further minimize attrition, the research team will send daily reminder messages via WhatsApp each morning, reinforcing engagement. Weekly live video calls will also serve to optimize exercise execution and encourage adherence.

**Video 1 VID1:** Instructional video demonstrating proper exercise techniques for patients in the home-based prehabilitation program.

Primary outcome

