In TKA, the extent of surgical trauma significantly influences postoperative pain and recovery. Plasma CRP, a well-established biomarker of tissue injury and inflammation, is commonly used to monitor recovery due to its rapid response, high specificity for acute inflammation, and ease of measurement, especially in elderly arthroplasty patients. CRP was selected as the primary outcome because of its association with osteoarthritis severity, surgical response, and postoperative complications, typically peaking on the third postoperative day [17].

Blood samples will be collected in an outpatient setting at four periods: before and after the eight-week prehabilitation program and three and 30 days post-TKA in both the experimental and control groups. The preoperative measurement one day before surgery (t3 in Figure 1) was timed to reflect chronic systemic adaptations resulting from prehabilitation while minimizing the confounding influence of acute exercise responses. This decision is supported by evidence showing that CRP typically returns to baseline (or a new post-exercise baseline) within six days after cessation of exercise [18]. The third postoperative day (t5) was selected to capture the peak inflammatory response following surgery, as supported by TKA-specific literature [17]. This time point also coincides with the typical hospitalization period, facilitating consistent, in-hospital sample collection. In the long term, given the anti-inflammatory effects of physical exercise, sustained reductions in CRP levels may reflect the effectiveness of the intervention in modulating systemic inflammation and promoting recovery [14].

Given that CRP levels can be influenced by factors such as sleep deprivation and acute infections, additional control measures will be implemented. Participants will report their average sleep duration and quality during the week preceding each blood draw (except for the third-day post-TKA measurement), as insufficient or disturbed sleep is associated with elevated CRP levels. Additionally, clinical symptoms suggestive of viral or bacterial infections (e.g., fever, sore throat, cough, or malaise) will be assessed before each collection since such conditions may increase CRP levels and confound the interpretation of the intervention's effects [19]. These precautions aimed to strengthen the internal validity of CRP as a primary outcome by minimizing interference from unrelated acute inflammatory processes.

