Adherence to the prehabilitation program will be assessed by calculating the percentage of completed sets compared to the total prescribed sets. This information will be recorded in the training diary and reported by the patient or a family member. The number and classification of adverse events occurring during the home-based training period will be recorded separately from hospital outcomes.

Adherence will be operationally defined as the completion of ≥75% of prescribed sessions, based on adherence rates commonly reported in the literature. A recent systematic review by Adebero et al. [7] found that most prehabilitation trials achieved adherence rates of 74% or higher, supporting the use of this threshold. This cutoff will be used to determine eligibility for per-protocol analyses evaluating intervention efficacy, while all randomized participants will be retained in the dose-response analysis, regardless of adherence level.

Hospital outcomes

Hospital outcomes will include the length of hospital stay (in days), hospital readmission rate, and number and classification of complications occurring within 30 days post-surgery. These indicators were selected to complement the biological and functional recovery metrics, offering system-level proxies for early recovery quality. Specifically, reduced length of stay may reflect improved physiological readiness for discharge, while lower readmission and complication rates may signal enhanced resilience and postoperative recovery. These data will be retrieved from patients’ medical records, which will be accessed using the registration number recorded during patient enrollment. Surgical complications will be defined as any adverse events based on the Clavien-Dindo classification [26].

Satisfaction level

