## Appendices

**Table 2 TAB2:** Training diary for patients to log weekly exercise frequency. The training diary will be given to patients at the baseline visit.

Workout 1					Date: __/__/____	
Exercise	Set 1	Set 2	Set 3	Difficulty		
Seated knee flexion and extension	( )	( )	( )	Easy ( )	Moderate ( )	Difficult ( )
Marching in place	( )	( )	( )	Easy ( )	Moderate ( )	Difficult ( )
Single-leg stance	( )	( )	( )	Easy ( )	Moderate ( )	Difficult ( )
Tandem walking (heel-to-toe)	( )	( )	( )	Easy ( )	Moderate ( )	Difficult ( )
Sit-to-stand	( )	( )	( )	Easy ( )	Moderate ( )	Difficult ( )
Wall calf raises	( )	( )	( )	Easy ( )	Moderate ( )	Difficult ( )

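### Adverse events before surgery are not clearly recorded in both arms, and regular contact is described for the experimental arm only, so harms in the exposure period could not be compared fairly

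*Protocol article*

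**What the plan says.** Under Prehabilitation adherence, after the diary-based adherence measure, the article states: "The number and classification of adverse events occurring during the home-based training period will be recorded separately from hospital outcomes". No arm is named, and no method of asking and no attribution rule are given.

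The Control group section says: "Participants in the control group will only follow these institutional procedures and will not engage in a home-based program". Controls receive a booklet and keep to their usual activities.

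The Experimental group section describes contact during the programme: "weekly videoconference sessions provide real-time feedback, while WhatsApp monitoring facilitates communication". It adds daily reminders, and it says the research team will "monitor any changes in the participants' physical or mental conditions". No comparable contact is described for controls between baseline and the pre-operative visit.

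Hospital outcomes covers complications within 30 days after surgery, taken from medical records. The analysis text under Results compares those complications between groups. It lists no comparison of events before surgery.

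**The concern.** The eight weeks before surgery are the only time when the two arms are treated differently by design, so any harm of the exercise programme itself would first appear then. Patients with advanced knee osteoarthritis can have falls, joint flares and intercurrent illness whether or not they exercise. A count of such events can be read only against a control count obtained in the same way.

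If one arm is asked every week and the other is not asked until surgery, a difference in recorded events mixes programme harm with intensity of looking. The trial means to inform public implementation of a programme done largely at home, and readers will want to know what it did to patients before their operation.

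**Working it through.** The plan states no figure on this point, so the check sets the sections side by side and then adds an illustration under stated assumptions.

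**1. Who is covered?** There are two readings of the sentence in Prehabilitation adherence.
- *Experimental arm only.* The sentence stands in the adherence section and names the period after a programme that controls do not follow. For blood sampling, the Primary outcome section names both arms: "before and after the eight-week prehabilitation program and three and 30 days post-TKA in both the experimental and control groups". The adverse event sentence has no such phrase.
- *A shared calendar window.* The same Primary outcome wording uses the programme as a time marker for both arms, so the adverse event sentence could do so too.

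The text does not settle which is meant.

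**2. Does the shared-window reading remove the problem?** No. Every described route by which an event would surface during those weeks (weekly call, WhatsApp, observation of condition) is in the Experimental group section. The windows could match while the intensity of ascertainment still differed.

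**3. Do other two-arm data fill the gap?** Only in part.
- Primary outcome: "clinical symptoms suggestive of viral or bacterial infections (e.g., fever, sore throat, cough, or malaise) will be assessed before each collection". This covers infection symptoms only, collected as a confounder of CRP.
- WOMAC before hospitalisation shows pain, stiffness and function on one occasion. It does not record falls, injuries, cardiac or respiratory events, or unplanned care.
- The withdrawal and exclusion rules under Enrollment presuppose that some events become known, but they describe no record of them by arm.
- Hospital outcomes begin with surgery.

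**4. Illustration.** Assumptions: 86 participants (Sample size section) split evenly, so 43 per arm; the same true background risk p in both arms; no exercise effect. The documents do not give p, so the range 5% to 30% is used.
- Expected background events in the experimental arm = 43 × p: 43 × 0.05 = 2.15 and 43 × 0.30 = 12.9, so about 2 to 13.
- If the probability that an event is captured is c₁ in the experimental arm and c₀ in controls, the apparent excess is 43 × p × (c₁ − c₀). With a capture gap of 0.5 this is 1.1 to 6.5 events. With no gap it is zero. The gap is unknown, so these figures show the mechanism and do not predict a result.

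**5. What symmetric recording could deliver.** With risk p in each arm, the approximate 95% half-width for the difference is 1.96 × √(2p(1−p)/43):
- p = 0.05: 1.96 × 0.047 = 9.2 percentage points
- p = 0.10: 1.96 × 0.065 = 12.7 points
- p = 0.30: 1.96 × 0.099 = 19.4 points

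Two-sided 5% power at 43 per arm (normal approximation for two proportions) is about 34% (background 5%) down to 16% (background 30%) for a 10-point excess. For a 20-point excess it is about 75% down to 47%. Matched recording would therefore support an estimate, not a firm safety test.

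**The case against.** The strongest reply is that the sentence is neutral as to arm, that the article elsewhere uses the programme as a calendar window for everyone, and that a condensed article may leave adverse event forms and questioning schedules to the full protocol. Safety is also not a stated objective, and some pre-operative information is collected in both arms.

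Much of this stands, and it limits the point. A reader might infer several stronger things that the documents do not support:
- *That controls have no pre-operative recording at all.* The text does not say so. It only fails to say that they are covered.
- *That training-period events will be counted as harms of exercise.* No attribution rule is stated. Such events could be mistaken for programme harms, which is a weaker statement.
- *That the trial cannot compare harms.* Complications in the 30 days after surgery are compared between arms.
- *That events are missed because most sessions are not watched live, or because the diary has no event field.* A weekly call can cover the preceding week, participants can write at any time, and the diary is an adherence log that the text does not make the adverse event instrument.
- *That a spurious significant difference will be reported.* The plan lists no between-arm test of pre-operative events, and complete non-capture in controls would be an extreme assumption.

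The reply does not remove the unequal contact. The article states a recording window, names it after one arm's programme and describes regular contact in that arm alone. That is more than an omitted detail.

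**Conclusion.** The point holds as a design improvement, confined to the period between randomisation and surgery. As written, pre-operative adverse events would be ascertained unequally, whichever way the window is read. Harms during exposure could then not be compared fairly by arm.

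The size of the distortion cannot be derived from the documents. It depends on the background risk and on the capture gap, neither of which is given. Under an assumed risk of 5% to 30%, about 2 to 13 experimental participants would have an event with no exercise effect, and there would be no matched control count to set against them. The conclusion assumes that no parallel control-arm procedure exists in a fuller document that is not shown. If one does, the article needs only a clarifying sentence. The primary CRP analysis and the post-operative complication comparison are untouched.

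**What to change.** - Define the pre-operative adverse event window as randomisation to the day before surgery, in both arms.
- At the existing pre-operative visit (t3), or at withdrawal if that comes first, ask both arms the same short structured questions: falls, injury, new or worse joint pain needing care, infection, cardiac or respiratory event, unplanned care.
- Report these answers by randomised arm as risks and a difference with 95% confidence intervals. Say in advance that this is estimation and not a test of safety.
- Report events that come to light through video calls, WhatsApp or the diary separately, as description of the experimental arm.

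The cost is one short form at a visit that both arms already attend. The downside is recall over about eight weeks. Under the Blinding section participants and assessors know the allocation, and weekly contact may prompt recall better in the experimental arm, so ascertainment would be more nearly equal but not identical. The report should say so.

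### Efficacy is assigned to a per-protocol set that only the experimental arm can fail, no as-randomised comparison is named, and adherence is given in two units

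*Protocol article*

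**What the plan says.** All references are to the protocol article.

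- **Prehabilitation adherence** measures adherence by "calculating the percentage of completed sets compared to the total prescribed sets". The next paragraph states: "Adherence will be operationally defined as the completion of ≥75% of prescribed sessions". The threshold is supported by a systematic review that "found that most prehabilitation trials achieved adherence rates of 74% or higher".
- The same paragraph gives the cut-off its use: "This cutoff will be used to determine eligibility for per-protocol analyses evaluating intervention efficacy". It then says that "all randomized participants will be retained in the dose-response analysis, regardless of adherence level".
- **Results** (the statistical methods) specifies a group × time repeated-measures ANOVA for CRP, with a mixed model or GEE if assumptions fail, and t-tests or Mann-Whitney tests for the secondary outcomes measured at specific time points. No analysis population is given for any of these. The section ends by placing patients below the threshold, and those who withdrew because of comorbidities or frailty, in linear regression models of dose-response.
- **Control group**: "Participants in the control group will only follow these institutional procedures and will not engage in a home-based program".
- **Enrollment**: "Patients will be excluded if they fail to attend scheduled telerehabilitation sessions or respond to WhatsApp communication". Patients with unexpected medical complications are told to stop the programme and leave the study.
- **Experimental group**: three sessions a week for eight weeks, "totaling a maximum of 24 training sessions".

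Intention-to-treat, or any comparison of the arms as randomised, is not named anywhere.

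**The concern.** The only place where the article ties an analysis set to efficacy is the per-protocol sentence. The full randomised set is given a different job, a dose-response regression. Dose is chosen by the patient after randomisation, so that regression is not a comparison of the randomised arms, even if controls enter at dose zero.

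The cut-off acts on one arm. Controls have no prescribed sessions and all stay in, while experimental patients who exercise too little are removed. If adherence is related to prognosis or to change in CRP, the two groups compared are no longer exchangeable. The article itself links withdrawal to comorbidity and frailty, so such a relation is plausible.

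The Enrollment text makes it harder to assume that the unlabelled ANOVA includes everyone. It excludes patients who miss telerehabilitation sessions, which only experimental patients have, whereas the adherence and Results sections say that patients of this kind are retained.

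Finally, the set is not uniquely defined. Two units are used for adherence, and no rule says whether a partly done session counts.

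**Working it through.** **1. Do the two adherence units agree?**

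Table 1 lists 6 exercises of 3 sets each, so 6 × 3 = 18 sets per session. Over 24 sessions this is 24 × 18 = 432 sets. A 75% cut-off is 18 sessions or 324 sets.

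| Pattern | Sets | Sessions |
|---|---|---|
| 24 sessions, 2 of 3 sets of each exercise | 24 × 12 = 288; 288/432 = 66.7% | 24/24 = 100% if part sessions count |
| 18 sessions, 12 of 18 sets each | 18 × 12 = 216; 216/432 = 50% | 18/24 = 75% if part sessions count |
| 17 full sessions, 3 sets in each of the other 7 | 306 + 21 = 327; 327/432 = 75.7% | 17/24 = 70.8% if only full sessions count |

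The first two patients pass on sessions and fail on sets. The third does the reverse. Membership depends on the unit and on the missing rule for part sessions.

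**2. Numbers in the comparison**

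The target of 86 follows from 78 × 1.10 = 85.8. With 1:1 allocation, about 43 are expected per arm. If a share q of the experimental arm is removed, 43(1 − q) remain against 43 controls. The total 86 − 43q falls below the required 78 once q exceeds 8/43 = 18.6%, before any other loss.

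**3. Bias from screening one arm, with no true effect**

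Assumptions, none of them from the article: adherence and outcome are jointly normal with correlation r = 0.3, and q runs from 10% to 50%. With z the q-quantile of the standard normal and φ its density,

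bias in SD = r × φ(z) / (1 − q).

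- q = 10%: 0.3 × 0.1755 / 0.9 = 0.058
- q = 50%: 0.3 × 0.3989 / 0.5 = 0.239

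The mg/L column uses the SD of 10.95 quoted under Sample size. Type I error is for a two-sided two-sample t-test at 5%, by simulation.

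| q | Experimental n | Bias, SD | Bias, mg/L | Type I error, single time point |
|---|---|---|---|---|
| 10% | 38.7 | 0.058 | 0.64 | 5.7% |
| 20% | 34.4 | 0.105 | 1.15 | 7.1% |
| 30% | 30.1 | 0.149 | 1.63 | 9.1% |
| 40% | 25.8 | 0.193 | 2.12 | 11.6% |
| 50% | 21.5 | 0.239 | 2.62 | 14.2% |

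The result depends on r. Over q = 10-40%, letting r run from 0.2 to 0.5 gives bias of 0.04 to 0.32 SD and type I error of 5.4% to 25%.

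**4. The planned group × time test**

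The primary test is an interaction over four time points, so a shift common to all times cancels. Simulation with r = 0.3, q = 10-50% and no true effect gives:

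- adherence equally related to CRP at all four times: type I error about 5%, so no inflation;
- adherence related only to post-baseline CRP: about 6-14%. A repeat with within-patient correlation 0.5 and 20,000 trials per setting gave 5.5% at q = 10% and 13.0% at q = 50%.

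**The case against.** The strongest reply is that the article does not call the per-protocol analysis primary. The CRP analysis in Results carries no adherence restriction, and its fallback models are chosen partly because they cope with missing data. Strengths and limitations promises sensitivity analyses that account for adherence, which fits better with a main analysis not already limited to adherers. A condensed article may also leave population definitions to a fuller document. This stands in part. A reader might infer that the primary analysis is fixed as per-protocol, but the text does not say so; the primary population is unstated. What remains is more than silence, because the article positively attaches efficacy to the screened set and gives the full set another role.

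A reader might also take 74% as the average adherence and conclude that about half of the experimental arm would fail. The review is cited for a level that most trials reached or exceeded. That is neither a mean nor a distribution across individuals, so no failure rate can be derived from it.

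Nor can a reader assume that the bias must favour the intervention or must inflate the primary test. Direction depends on who adheres. The interaction test is inflated only if adherence tracks change in CRP.

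On units, one coherent reading is that sets measure the continuous dose and sessions set the cut-off. That is possible, but part sessions would still be undefined.

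**Conclusion.** The concern holds in a limited form. As written, efficacy conclusions can rest on adherers in one arm against everyone in the other, no comparison of the arms as randomised is named, and the exclusion wording conflicts with the stated retention.

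The size is uncertain. With r = 0.3 and 10-50% of the experimental arm removed, bias is about 0.06-0.24 SD. Type I error is about 5-15% at single time points, which is the form of the secondary comparisons. For the group × time test it is about 5% or about 6-14%, depending on whether adherence relates to CRP at all times or only after baseline. These figures illustrate a mechanism; the correlation and the share removed are assumptions, and the article gives neither.

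The ambiguity over sets and sessions is certain from the text but is the smaller part. It matters because it decides who belongs to the set to which efficacy is tied.

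**What to change.** 1. State that the primary CRP analysis and the secondary between-group comparisons include all randomised patients in their allocated arm. For CRP, use the linear mixed model already named, so that patients with partial data stay in.
2. Label the per-protocol and dose-response analyses as supportive. A complier-average causal effect, with randomisation as the instrument, is an optional alternative to the per-protocol comparison.
3. Use one adherence unit for the cut-off. The diary in Table 2 records each set, so a set-based rule (of 432) is already supported; a session-based rule would need a definition of a completed session.
4. Reconcile the exclusion and withdrawal wording under Enrollment with the retention stated under Prehabilitation adherence and in Results.

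The cost is mostly wording, but not entirely: outcome data must be kept for non-adherers. The headline effect may also be smaller than the per-protocol one.

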Patient satisfaction will be assessed 30 days post-TKA using a validated TKA satisfaction questionnaire [27]. This time point was selected to capture the short-term functional and symptomatic benefits of prehabilitation when effects on recovery are most tangible. Four primary questions, rated on a five-point Likert scale, will evaluate pain relief, functional improvement, and overall satisfaction. Scores ranged from 0 (very dissatisfied) to 100 (very satisfied), with the total score calculated as the mean of all responses. The total satisfaction score will be obtained by summing the individual scores of the four satisfaction questions and dividing by four. If any individual component is missing, the total score will not be calculated.

Sample size

The sample size was estimated using repeated measures analysis of variance with four time points (nine weeks pre-TKA, one day pre-TKA, three days post-TKA, and 30 days post-TKA) and two groups (experimental and control). Assuming a moderate effect size (f = 0.25), α = 0.05, and 80% power (β = 0.20), 78 participants were required (G*Power 3.1.9.7, University of Kiel, Germany). This effect size was selected based on evidence from a study in TKA patients with CRP as the primary outcome, which reported a between-group difference of 9.12 mg/L and a pooled standard deviation of 10.95, corresponding to a Cohen’s d of 0.83 (f ≈ 0.29), and statistical power of 88% with 61 participants. Therefore, f = 0.25 was adopted as a conservative and evidence-based estimate for the current trial [28]. Accounting for a 10% potential attrition rate, the final target sample size was 86 participants.

Blinding

This study follows a single-blind design, in which only the data analyst remains blinded to group allocation. Due to the nature of the intervention (an exercise program), blinding participants or intervention providers was not feasible, as doing so would compromise adherence, safety, and protocol fidelity. Consequently, participants, data collectors, and outcome assessors will be aware of group assignments.

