## Results

The significance level was set at p < 0.05, and analyses will be performed using IBM SPSS Statistics 21.0 (IBM®, Armonk, NY, USA). Data normality will be assessed using the Shapiro-Wilk test. Baseline demographic characteristics will be compared between the groups using independent t-tests (normal data), Mann-Whitney U tests (non-normal data), and chi-square or Fisher’s exact tests (categorical variables).

The primary outcome, changes in plasma CRP levels across four time points (nine weeks pre-TKA, one day pre-TKA, three days post-TKA, and 30 days post-TKA), and WOMAC scores across three time points (baseline, one day pre-TKA, and 30 days post-TKA) will be analyzed using two-way repeated-measures ANOVA (group × time interaction), contingent upon assumptions of normality and sphericity. If these assumptions are violated, linear mixed models (LMM) or generalized estimating equations (GEE) will be employed as more robust alternatives, capable of handling missing data and irregular intervals. Post-hoc pairwise comparisons will use the Bonferroni correction to adjust for type I errors. For non-parametric repeated measures, the Friedman test will be used, followed by Dunn-Bonferroni post-hoc tests when applicable.

Secondary outcomes, including synovial fluid and tissue biomarkers, hospital outcomes (length of stay, complications, readmissions), and satisfaction scores at specific time points, will be compared between groups using independent t-tests (normal data) or Mann-Whitney U tests (non-normal data). Correlations between biomarkers, hospital outcomes, WOMAC scores, and satisfaction will be examined using repeated measures correlation (rmcorr) for normal data or generalized linear mixed model (GLMM) for non-normal data. Rmcorr will be applied when assessing the strength and direction of associations between two continuous variables measured repeatedly within individuals. GLMM will be used in cases requiring the modeling of random effects, adjustment for covariates, or handling of non-normal or categorical outcomes, ensuring analytic flexibility across diverse data structures. To account for multiple comparisons in biomarker and exploratory analyses, false discovery rate (FDR) adjustment will be applied where appropriate.

Effect sizes (e.g., partial eta-squared for ANOVA and Cohen’s d for pairwise tests) and 95% confidence intervals will be reported alongside p-values to enhance the clinical interpretability of findings.

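### The sample-size paragraph converts d = 0.83 to the wrong f, gives a 78 that cannot be traced to the group × time test, and calls f = 0.25 conservative on a scale that does not match that test

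*Protocol article*

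**What the plan says.** All the planning figures are in the protocol article, Materials and methods, Sample size.

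- Method: "The sample size was estimated using repeated measures analysis of variance with four time points" and two groups.
- Inputs and result: "Assuming a moderate effect size (f = 0.25), α = 0.05, and 80% power (β = 0.20), 78 participants were required", computed in G*Power.
- Source of the effect size: a study in TKA patients with CRP as primary outcome, which "reported a between-group difference of 9.12 mg/L and a pooled standard deviation of 10.95", summarised as "d of 0.83 (f ≈ 0.29), and statistical power of 88% with 61 participants".
- Conclusion drawn: "f = 0.25 was adopted as a conservative and evidence-based estimate for the current trial".
- Attrition: "Accounting for a 10% potential attrition rate, the final target sample size was 86 participants".

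The Results section then states the primary analysis: CRP over four time points "will be analyzed using two-way repeated-measures ANOVA (group × time interaction"), on condition that normality and sphericity hold. If they do not, mixed models or estimating equations replace the ANOVA. The Sample size section does not say which repeated-measures effect was powered, nor which effect-size option, correlation among measurements or epsilon was used.

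**The concern.** Four statements in one paragraph do not fit together.

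1. The printed f does not match the printed d.
2. The printed 78 does not match the printed inputs for the test that will be run.
3. A standardised difference between two groups is compared directly with an effect size for a repeated-measures test, as if both were on one scale. The word conservative rests on that comparison.
4. The attrition allowance falls just short of the number it is meant to protect.

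What is at stake is the meaning of the stated 80% power. As printed, it cannot be tied to an identified hypothesis or to a CRP difference in mg/L. A reader therefore cannot tell what the trial was designed to detect.

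**Working it through.** **Inputs from the article.** Difference 9.12 mg/L, SD 10.95, source study of 61 participants with 88% power, f = 0.25, α = 0.05, power 80%, two groups allocated 1:1, m = 4 time points, N = 78, attrition 10%, target 86. **Assumed, because not stated:** equal arms (30 and 31 in the source study), correlation ρ and epsilon ε over the ranges shown.

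**Step 1: conversion.**
- d = 9.12/10.95 = 0.833, which reproduces the printed 0.83.
- For two equal groups f = d/2 = 0.416, or 0.42. The printed 0.29 equals d/(2√2) = 0.294, which is not the two-group conversion.
- Check against the quoted power (two-sided t test, 30 v 31): d = 0.833 gives 89%, close to the printed 88%. With f = 0.29, d = 0.58 and power is 61%. The paragraph's own power figure therefore supports 0.42.

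**Step 2: can 78 be reproduced?** For the group × time interaction under G*Power's default option, λ = N f² m ε/(1−ρ), with 3ε and 3(N−2)ε degrees of freedom. Example: N = 24, ρ = 0.5, ε = 1 gives λ = 24 × 0.0625 × 4/0.5 = 12 and power 82%.

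| Effect and option (f = 0.25, 80% power) | Setting | N |
|---|---|---|
| Interaction, default | ρ = 0.7, ε = 1 | 16 |
| Interaction, default | ρ = 0.5, ε = 1 | 24 |
| Interaction, default | ρ = 0.3, ε = 1 | 32 |
| Interaction, default | ρ = 0, ε = 1 | 46 |
| Interaction, default | ρ = −1/3 (lowest admissible), ε = 1 | 60 |
| Interaction, 'as in SPSS' | ε = 1 | 62 |
| Interaction, 'as in SPSS' | ε = 0.7 | 78 |
| Interaction, default | ρ = 0, ε = 0.45 | 78 |
| Between-group main effect | ρ = 0.5 | 82 |
| Between-group main effect | ρ = 0.46 to 0.47 | 78 |

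Under sphericity (ε = 1) no correlation gives 78 for the interaction. The 78 can be reached, but only with an unstated epsilon well below 1, or by powering a main effect that is not the planned test.

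**Step 3: is f = 0.25 conservative for an interaction?** If a difference of d SD is present at a fraction p of the four times and absent at the others, the interaction effect is f = (d/2)√(p(1−p)).
- Day 3 only (p = 1/4), or sustained at all three later times (p = 3/4): f = 0.416 × √(3/16) = 0.416 × 0.433 = 0.18.
- Two of four times (p = 1/2): f = 0.416 × 0.5 = 0.21.

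Both are below 0.25. In the first two profiles f = 0.25 would require d = 0.25/0.2165 = 1.15, that is 1.15 × 10.95 = 12.6 mg/L, which is larger than the cited 9.12.

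**Step 4: power of 78 patients for the cited difference.** Interaction test, d = 0.83, f = 0.18:

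| ρ | ε = 1 | ε = 0.7 |
|---|---|---|
| 0 | 76% | 65% |
| 0.3 | 90% | 81% |
| 0.5 | 97% | 92% |
| 0.7 | over 99% | 99% |

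**Step 5: attrition.** The 86 is reproduced by 78 × 1.10 = 85.8. But 86 × 0.90 = 77.4, below 78. The required inflation is 78/0.90 = 86.7, so 87, and 87 × 0.90 = 78.3.

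**The case against.** The strongest reply has five parts.

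- **The f error does no harm to N.** This stands. The calculation uses 0.25, and on the two-group scale correcting 0.29 to 0.42 puts 0.25 further below the source value. The printed figure is still wrong.
- **Correlation, epsilon and the effect-size option are details that a journal article may leave to the full protocol.** This largely stands, and their absence alone would be no finding. A reader might infer that 78 is wrong or impossible. The documents do not support that: the 'as in SPSS' option with ε = 0.7 gives 78 for the interaction, and the planned software is SPSS. What remains is that the inputs the article does print, with the test it names, lead elsewhere. An ε of 0.7 would also describe data for which the Results section replaces the ANOVA.
- **The trial has enough power.** A reader might infer from Step 3 that it is underpowered. Step 4 does not show this: for the only CRP difference the article cites, power is at or above 80% except at low correlation.
- **A null result remains interpretable.** This stands. The Results section commits to effect sizes and 95% confidence intervals, which show what a null result excludes whatever the planning paragraph says.
- **The attrition gap is one patient, from a common shortcut.** This stands; it is worth correcting only because the paragraph needs rewriting anyway.

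**Conclusion.** The concern holds as a reporting and traceability fault, of minor to moderate severity.

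- **Firm:** d = 0.83 is f = 0.42 for equal groups, not 0.29, and the article's own 88% power contradicts 0.29. Also firm, but minor: 86 less 10% leaves 77.
- **Firm within its limits:** 78 does not follow from the stated inputs for the group × time test under sphericity. It is untraceable, not shown to be wrong.
- **Conditional on the assumed profiles:** the cited difference is an interaction f of 0.18 to 0.21, so conservative is unsupported for the planned test. The article states no profile that would rescue the word.

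None of this shows that the trial is too small, or that the primary test should be replaced. The power figures assume normal data, equal arms, a common correlation and the source SD of 10.95 at every time point.

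**What to change.** Rewrite the Sample size paragraph and keep the stated primary test.

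1. Replace f ≈ 0.29 with f = 0.42 for d = 0.83.
2. Name the effect, effect-size option, correlation and epsilon that gave 78. If they cannot be recovered, state instead the power of 78 patients for the group × time test at the cited 9.12 mg/L, with the assumed time profile and a range of correlations and epsilon, as in Step 4.
3. Remove the word conservative, or justify it on the interaction scale.
4. State that 86 recruited yields 77 analysed, or set the target at 87.

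The cost is one rewritten paragraph and at most one additional participant. It is best done before the data are analysed, so that the power claim is settled independently of the results.
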